## Abstract

**Introduction:**

Delta waves (0.1–4 Hz) are a hallmark of unconsciousness in both sleep and general anesthesia (GA). Closed-loop auditory stimulation (CLAS) delivers brief sounds phase-locked to ongoing slow oscillations and can modulate slow-wave activity (SWA) during sleep, but its efficacy and translational relevance under propofol anesthesia, particularly in the presence of nociceptive input, remain unknown.

**Methods:**

We describe a prospective, within-subject protocol in 30 neurologically healthy adults undergoing elective surgery under propofol GA. Intraoperative high-density electroencephalography (hd-EEG; 128 channels) is recorded while a real-time CLAS algorithm detects *δ*-waves at the Fz electrode, and triggers pink-noise bursts in three conditions: *in-phase* (peak-locked), *anti-phase* (trough-locked), and *sham*. An extended *in-phase* block is then combined with a standardized tetanic nociceptive stimulus (100 Hz, 70 mA, 30 s) to test robustness under an arousal challenge. Depth of hypnosis is monitored with the Bispectral Index (BIS), and nociceptive/autonomic reactivity with the Nociception Level (NOL) index. Primary outcomes quantify *δ*-wave morphology and SWA (amplitude, slopes, duration/frequency, transition frequency, density, power spectral density), along with topography, source estimation, and propagation. Secondary outcomes include depth of anesthesia (BIS), nociceptive balance (NOL), functional connectivity (weighted and directed phase-lag indices), graph-theoretical organization (global efficiency, clustering, modularity, small-worldness), and EEG microstates (duration, coverage, transitions).

**Discussion:**

If confirmed, these findings would position CLAS as a candidate neuromodulation strategy to reinforce anesthetic *δ*-wave dynamics and help stabilize anesthesia without necessarily increasing pharmacological dose, while also providing a systems-level test of the role of slow oscillations in sustaining unconsciousness.

## Introduction

1

### From sleep to anesthesia: a shared neurophysiological landscape

1.1

General anesthesia (GA) is often colloquially described as “falling asleep.” Although sleep and anesthesia arise from distinct mechanisms, they share striking neurophysiological signatures. Both are associated with a reversible loss of awareness, diminished sensory processing, and unresponsiveness to external stimuli (Brown et al., 2010; Murphy et al., 2011; Purdon et al., 2013). A central commonality is the presence of synchronized low-frequency activity in the electroencephalogram (EEG), most prominently within the delta frequency range (0.1–4 Hz) (Massimini et al., 2004; Steriade et al., 1993). This convergence has motivated extensive comparisons between anesthesia, sleep, and coma in the neuroscience of consciousness (Akeju and Brown, 2017; Bonhomme et al., 2016; Boveroux et al., 2010; Mashour, 2024; Mashour and Hudetz, 2018).

Within the delta band, two related but distinct phenomena can be identified: slow oscillations (SOs; <1 Hz) and slow waves (SWs; 1–4 Hz) (Massimini et al., 2004; Steriade et al., 1993). SOs are large-amplitude, <1 Hz oscillations representing the alternation between cortical up- and down-states, and are considered the fundamental rhythm of deep non-rapid eye movement (NREM) sleep (Sanchez-Vives and McCormick, 2000; Steriade et al., 1993a, 1993b). In contrast, SWs are faster oscillations in the delta band that often co-occur with SOs but may involve partially distinct synchronization mechanisms, especially thalamocortical contributions (Timofeev and Chauvette, 2011). Together, SOs and SWs form the backbone of the EEG slow-wave activity (SWA) that typifies both deep sleep and anesthesia. For clarity, in the remainder of this manuscript we will use the term “*δ*-waves” to collectively refer to SOs and SWs, unless explicitly distinguished. Here we adopt a slightly broadened delta range (0.1–4 Hz) to encompass very slow fluctuations approaching the classical SO band.

### SOs and SWs in anesthesia

1.2

Loss of behavioral responsiveness during anesthesia is often accompanied by enhanced SO and SW activity, particularly under the GABAergic agent propofol (Purdon et al., 2013; Murphy et al., 2011). As established in sleep research, SOs and SWs represent distinct but interacting components of delta-band activity, relying on partially different synchronization mechanisms. Under anesthesia, these same oscillatory motifs are preserved in form but are generated and stabilized through pharmacological rather than endogenous network dynamics (Brown et al., 2011; Franks, 2008; Murphy et al., 2011).

In natural sleep, SOs are generated primarily within the neocortex through recurrent excitatory–inhibitory interactions that produce alternating up-states of widespread depolarization and down-states of near-silence across large neuronal populations (Sanchez-Vives and McCormick, 2000; Steriade et al., 1993b). These oscillations propagate as traveling waves across the cortical surface, typically in an anterior-to-posterior direction (Cox et al., 2014; Massimini et al., 2004). While the thalamus is not required for SO initiation, it contributes to their synchronization and amplification via thalamocortical loops (Timofeev and Chauvette, 2011). Under propofol anesthesia, SOs continue to reflect large-scale cortical up–down state alternations, but their dynamics are pharmacologically enforced rather than self-organized. Propofol potentiates GABA-A–mediated inhibition, stabilizing cortical bistability and prolonging down-states, resulting in highly regular, high-amplitude SOs (Brown et al., 2011; Franks, 2008). These anesthetic SOs display striking similarities to those observed during deep NREM sleep, including frontal predominance and anterior-to-posterior propagation, yet with more diffuse initiation sites and stronger interhemispheric symmetry (Franks and Zecharia, 2011; Massimini et al., 2004; Murphy et al., 2011; Lee et al., 2013).

In contrast, SWs rely more often on thalamocortical mechanisms. In sleep, SWs are frequently nested within an SO cycle but reflect higher-frequency delta activity shaped by thalamocortical bursting: hyperpolarization of thalamic relay neurons promotes rhythmic low-threshold calcium spikes that reinforce cortical rhythms (Steriade et al., 1993b; Timofeev and Chauvette, 2011). Under GABA-A-potentiating agents such as propofol, this thalamocortical drive is further stabilized by drug-induced hyperpolarization (Franks, 2008; Brown et al., 2011). Some propofol studies have reported that SWs may originate from more spatially diffuse cortical hotspots and to exhibit more regular temporal dynamics compared with natural NREM sleep (Murphy et al., 2009; Murphy et al., 2011).

### General anesthesia: pharmacology and monitoring

1.3

GA is a pharmacologically induced, reversible state that enables surgery by combining four key components: hypnosis (loss of consciousness), analgesia (absence of pain), amnesia (lack of memory), and immobility (muscle relaxation) (Brown et al., 2010; Sessler et al., 2012). The concept of balanced anesthesia is to achieve these components through the synchronized administration of smaller, safer doses of multiple agents, thereby reducing the adverse effects that arise from high doses of a single drug (Lundy, 1926; Sessler et al., 2012).

Among these agents, propofol is the most widely used intravenous anesthetic for induction and maintenance of hypnosis. Its primary mechanism is potentiation of the inhibitory GABA-A receptor, leading to neuronal hyperpolarization and reduced excitatory transmission across cortical and thalamic networks (Brown et al., 2010; Franks, 2008). Propofol reliably produces unconsciousness and is strongly associated with the enhancement of SWA, though its effects are dose-dependent: higher concentrations prolong down-states, increase the risk of burst suppression, and can cause cardiovascular depression (Murphy et al., 2011; Purdon et al., 2013).

During GA, particularly its hypnotic and amnestic components, there is no direct clinical sign that reliably indicates the depth of anesthesia. In routine practice, anesthesiologists therefore rely on measured concentrations of volatile anesthetic agents or on predicted effect-site concentrations for intravenous drugs to titrate anesthetic depth. While these pharmacokinetic parameters provide a rough estimate of drug delivery and effect, they do not directly reflect the underlying neural state of unconsciousness, which can vary considerably between individuals despite similar concentrations. To complement these measures, several EEG-based neuromonitoring devices have been developed to provide real-time indices of anesthetic depth.

The Bispectral Index (BIS; Rampil, 1998; Sigl and Chamoun, 1994) is one of the most widely used EEG-based monitors. The BIS algorithm extracts spectral and bispectral features from a frontal EEG signal, quantifying both the power distribution and phase relationships between frequency components, and integrates these into a single index ranging from 0 (isoelectric EEG) to 100 (fully awake). Clinically, values between 40 and 60 are typically targeted to maintain surgical anesthesia. While BIS monitoring has proven useful in reducing the risk of awareness and optimizing anesthetic titration, it remains an indirect measure of brain state, reflecting correlates of anesthetic depth rather than the underlying neuronal mechanisms of unconsciousness. The SedLine^®^ (Masimo Corporation, Irvine, CA, United States) system provides an alternative EEG-based approach to monitoring anesthetic depth. It uses a four-channel frontal EEG montage to compute the Patient State Index (PSI), a 0–100 scale with lower values indicating deeper hypnosis (Drover et al., 2002; Drover and Ortega, 2006; Prichep et al., 2004).

To maintain safe and effective anesthesia, and intraoperative nociception, clinicians traditionally monitor various physiological and clinical markers such as changes in heart rate and blood pressure, alterations in respiratory rate and pattern, pupil size and reactivity, the presence of lacrimation or sweating, variations in muscle tone or spontaneous movement, and other autonomic responses such as flushing or tachycardia. In parallel, some clinicians have started using an emerging device called the Nociception Level (NOL) index, a finger sensor which integrates autonomic signals, including heart rate variability, skin conductance, and photoplethysmography, to provide a real-time estimate of nociceptive processing during surgery (Ben-Israel et al., 2013).

Together, EEG-based indices of hypnotic depth (BIS and PSI) and autonomic measures of nociception (NOL) allow anesthesiologists to titrate anesthetic and analgesic agents in a patient-specific manner, maintaining a safe balance between unconsciousness and analgesia while minimizing complications such as hemodynamic instability, intraoperative awareness, or delayed recovery (Garcia-Larrea and Bastuji, 2018; Mashour et al., 2012; Willingham et al., 2014).

### Interactions between nociception and consciousness

1.4

In GA, each component interacts dynamically together rather than acting independently. In particular, nociception and consciousness are biologically intertwined. While unconsciousness prevents the subjective experience of pain, nociceptive input continues to activate ascending neural pathways, influencing cortical and subcortical dynamics even under anesthesia (Garcia-Larrea and Bastuji, 2018).

The primary pathway for nociceptive processing originates with peripheral nociceptors, which transmit signals through the spinothalamic tract to the thalamus and subsequently to cortical regions including the insula, the anterior cingulate cortex, and somatosensory cortices (Apkarian et al., 2005). Importantly, these same structures contribute to arousal regulation and awareness, meaning that nociceptive signaling can act as an arousal stimulus capable of modulating the depth of hypnosis (Brown et al., 2010; Garcia-Larrea and Bastuji, 2018). Functional imaging and EEG studies have shown that nociceptive input during anesthesia can transiently increase cortical responsiveness and disrupt ongoing SW dynamics, suggesting a mechanistic basis for nociception-induced lightening of unconsciousness (Bonhomme et al., 2016; Plourde et al., 2006).

This interaction has direct clinical consequences. Inadequately controlled nociception during anesthesia can provoke sympathetic activation, leading to hemodynamic disturbances such as hypertension and tachycardia (Brown et al., 2010). Conversely, excessively high doses of hypnotics used to suppress nociceptive arousals can result in cardiovascular depression and burst suppression, both of which are associated with poor postoperative outcomes (Sessler et al., 2012; Willingham et al., 2014). Thus, modern balanced anesthesia requires continuous assessment of both hypnotic depth and nociceptive state, underscoring the clinical importance of integrating monitors such as the BIS and the NOL index (Ben-Israel et al., 2013; Lewis et al., 2019).

### Closed-loop auditory stimulation as a modulator of delta waves

1.5

SWA plays critical roles in sleep physiology, including memory consolidation, metabolic clearance, and the dissipation of homeostatic sleep pressure (Fultz et al., 2019; Krueger et al., 2016). Declines in SWA are consistently linked to aging and neuropsychiatric disorders such as depression, schizophrenia, and dementia (Baglioni et al., 2016; Scullin, 2013). Over the past decade, closed-loop auditory stimulation (CLAS) has emerged as a powerful method to modulate SWA in real time. By delivering auditory stimuli phase-locked to ongoing SOs, CLAS can selectively enhance their amplitude and slope when applied on the ascending phase of SOs, right before the positive peak (called “*in-phase*” or “*peak*” stimulation; Ngo et al., 2013; Ngo et al., 2015). Conversely, stimulation during the descending phase, after the positive peak but before the negative peak (called “*anti-phase*” or “*trough stimulation*”) tends to disrupt SWA expression (Navarrete et al., 2020; Ngo et al., 2013). Thus, the precise timing of auditory stimulation is crucial: it can either reinforce or attenuate the manifestation of SOs, depending on the phase of delivery. Importantly, CLAS effects have been shown to be primarily stimulus-locked and self-limited: phase-locked auditory clicks transiently amplify the targeted SO, but do not induce sustained modulation beyond the directly stimulated oscillatory cycles (Ngo et al., 2013; Ngo et al., 2015).

Across sleep studies, *in-phase* CLAS has been shown to modulate slow oscillatory activity and, in several cases, enhance sleep quality and declarative memory consolidation (Diep et al., 2021; Ngo et al., 2013; Ngo et al., 2015; Ong et al., 2016; Papalambros et al., 2017). However, other studies have reported no significant effects on memory outcomes (Henin et al., 2019; Ong et al., 2018), suggesting that the cognitive benefits of CLAS may depend on task type, stimulation parameters, and individual responsiveness. In a multi-night paradigm, repeated CLAS was associated with improvements in sleep continuity and memory performance, and with stimulation-response–dependent associations with plasma amyloid biomarkers (Aβ42/Aβ40 ratio), suggesting that sustained SW reinforcement can engage sleep-dependent physiological processes beyond acute EEG modulation (Zeller et al., 2024).

The effectiveness of this technique relies on the intact transmission of auditory signals through the peripheral and central auditory pathways, beginning with cochlear activation and propagation via the vestibulocochlear nerve (cranial nerve VIII) to higher-order cortical regions (Bellesi et al., 2014; Esfahani et al., 2023; Ngo et al., 2013). Studies suggest that these signals ascend predominantly through the non-lemniscal pathway and reach higher-order associative regions, where they evoke event-related potentials in response to sound (Atienza et al., 2001; Hu, 2003; Jourde et al., 2023). Previous EEG and fMRI studies have confirmed that the brain retains its ability to process auditory stimuli during deep states of anesthesia (Hartikainen and Rorarius, 1999; Nourski et al., 2017; Plourde et al., 2006). These findings suggest that the necessary sensory and cortical pathways required for CLAS remain functional under anesthesia, providing a neurophysiological basis for exploring whether CLAS can effectively modulate anesthetized brain states.

Auditory stimulation is particularly well suited for closed-loop modulation of SOs under anesthesia for several reasons: auditory stimulation at low intensity offers a simple, non-invasive, and temporally precise approach for engaging slow oscillatory dynamics, with minimal interference with the surgical field. In sleep, auditory stimuli are well known to evoke K-complex–like responses that share core morphological and generative features with SOs and rely on corticothalamic circuitry involved in *δ*-wave generation (Cash et al., 2009; Colrain, 2005). Under propofol anesthesia, early auditory cortical responses and thalamocortical relay activity are suppressed but not abolished, providing a preserved pathway through which phase-locked auditory input may interact with drug-stabilized δ oscillations. This preserved auditory–corticothalamic coupling provides a mechanistic rationale for using auditory stimulation, rather than other sensory modalities, to probe and modulate slow oscillatory activity under general anesthesia (Ngo et al., 2013; Nourski et al., 2017).

The mechanistic differences between SWs and SOs are directly relevant for interpreting CLAS effects under anesthesia. Whereas SOs primarily index large-scale cortical synchronization and traveling-wave dynamics, SWs reflect the strength and stability of thalamocortical bursting and cortico-thalamic coupling. Consequently, CLAS-induced changes in δ-wave expression may differentially reflect modulation of cortical up–down state timing, thalamocortical engagement, or their interaction, depending on which oscillatory features are most affected.

In the present protocol, SOs and SWs are not separated, and CLAS targets *δ*-waves broadly within the 0.1–4 Hz range. This choice reflects both methodological and physiological considerations. To date, CLAS has not been applied under general anesthesia, and no prior work has established whether SOs and SWs can or should be differentially targeted in this pharmacologically stabilized state. Accordingly, the present protocol targets *δ*-waves to capture the full spectrum of propofol-induced slow activity and maximize sensitivity to stimulation effects in this unexplored context. Nevertheless, distinguishing between these oscillatory components remains conceptually important for interpreting whether CLAS preferentially modulates cortical synchronization, thalamocortical drive, or a combined contribution to general anesthesia unconsciousness.

### Translating CLAS beyond natural sleep

1.6

Recent work has extended CLAS beyond natural sleep into pharmacological sedation, demonstrating its potential to modulate *δ*-waves in altered states of consciousness. The CLASS-D protocol (Guay et al., 2021) is a within-subject, crossover, controlled trial in healthy volunteers designed to test whether SWA under dexmedetomidine sedation can be enhanced via closed-loop acoustic stimulation (*in-phase, anti-phase*, and *sham* conditions), with high-density EEG recording and assessments of subsequent sleep architecture. The more recent study by Smith et al. (2024) implemented that protocol and reported that daytime dexmedetomidine sedation paired with *in-phase* CLAS alters slow-wave homeostasis: specifically, it induced sleep-like states that fulfilled certain homeostatic NREM sleep needs, reduced N3 duration on the post-sedation night, and modified dissipation of slow-wave pressure compared to *anti-phase* CLAS. Thus, while Guay et al. (2021) laid out the methods and aims, Smith et al. (2024) provide empirical evidence that those methods produce measurable effects. Together, these studies indicate that CLAS can not only be feasibly applied under sedation with dexmedetomidine but also meaningfully alter SW dynamics and sleep homeostasis. Unlike sedation, GA with propofol represents a deeper state of unconsciousness with stronger drug stabilization and routine nociceptive input, making it a critical testbed for evaluating whether CLAS can reliably enhance *δ*-waves under surgical conditions.

### Study rationale

1.7

CLAS can augment SWs in sleep (Malkani and Zee, 2020; Ngo et al., 2013; Zeller et al., 2024) and has shown feasibility during pharmacological sedation using dexmedetomidine (Guay et al., 2021; Smith et al., 2024), but it remains unknown whether CLAS can enhance SWA under propofol GA, which is a deeper, drug-stabilized state that routinely includes nociception.

Mechanistically, CLAS is hypothesized to interact with propofol-induced *δ*-waves by moving through preserved auditory-corticothalamic pathways to deliver precisely timed stimulations to ongoing cortical activity. Auditory stimuli evoke time-locked cortical responses that transiently engage corticothalamic circuitry implicated in *δ*-wave generation. When delivered during the ascending phase of *δ*-waves, this stimulation is expected to bias the timing and synchronization of cortical up-down state transitions, increasing δ-wave amplitude. Conversely, stimulation delivered during the descending phase is expected to interfere with these transitions, leading to attenuation of the δ-wave amplitude. Under propofol anesthesia, where cortical and thalamocortical networks are pharmacologically stabilized, such phase-specific perturbations provide a principled mechanism by which CLAS may modulate δ-wave dynamics without increasing anesthetic dose.

Demonstrating SWA enhancement with CLAS during propofol anesthesia, without increasing hypnotic dose and while preserving physiological stability (hemodynamics, oxygenation), would suggest a viable non-pharmacological method to support balanced anesthesia.

### Objectives and hypothesis

1.8

The primary objective of this study is to determine whether CLAS can modulate *δ*-waves (0.1–4 Hz) during propofol-induced GA. Our central hypothesis is that CLAS can effectively enhance δ-waves during surgical anesthesia, and that this modulation will co-occur with changes in EEG/network features commonly observed in more stable anesthetized dynamics, while remaining inferential with respect to consciousness. While propofol enforces *δ*-waves dynamics via GABA-A potentiation (Brown et al., 2011; Franks, 2008), nociceptive input can still engage ascending pathways and modulate cortical state, challenging the maintenance of hypnosis (Brown et al., 2010; Garcia-Larrea and Bastuji, 2018). Consequently, our secondary objective is to assess whether the modulatory effects of *in-phase* CLAS on *δ*-waves during general propofol anesthesia are preserved in the presence of nociceptive inputs. Because nociception has been shown to interact with cortical arousal systems and transiently disrupt slow-wave dynamics (Bonhomme et al., 2016; Garcia-Larrea and Bastuji, 2018; Plourde et al., 2006), demonstrating that CLAS maintains or augments SWA under these conditions would provide critical translational evidence for its potential intraoperative application.

We will test these objectives through the following specific aims:

*Specific Aim 1 (SA1): Characterize the effect of in-phase and anti-phase CLAS on δ-wave morphology and topography, relative to sham stimulation*. We hypothesize that *in-phase* CLAS will increase amplitude, slope, duration, and density of δ-waves, decrease frequency and transition frequency, and will increase SWA power compared to *sham*. This effect will be most pronounced over frontal derivations, and will propagate posteriorly. We hypothesize that *anti-phase* CLAS will disrupt the intrinsic timing and propagation of δ-waves compared with *sham*, resulting in reduced amplitude, flatter slopes, lower transition frequency and decreased SWA power.

*Specific Aim 2 (SA2): Characterize the effect of in-phase CLAS on depth of anesthesia, as assessed through clinical monitoring tools and high-density EEG*. We hypothesize that *in-phase* CLAS will be associated with EEG and BIS changes indicative of altered anesthetic depth. At the network level, we expect *in-phase* CLAS to be associated with decreased functional connectivity within fronto-parietal circuits, reduced network integration, and increased modular segregation, consistent with a transition toward deeper unconsciousness. Microstate analyses are expected to reveal longer mean durations and reduced repertoire diversity, further reflecting a state of reduced dynamical complexity.

*Specific Aim 3 (SA3): Characterize the effect of in-phase CLAS on δ-waves, in the presence of painful stimulation*. We hypothesize the *in-phase* CLAS will enhance SWA in the presence of nociceptive stimulation, mitigating nociception-induced reductions in *δ*-wave dynamics. We expect this enhancement to be less pronounced than under non-nociceptive conditions, yet sufficient to mitigate nociception-induced reductions in δ-wave dynamics. Specifically, we will assess δ-wave amplitude, slope, frequency, transition frequency, duration, and density, as well as the preservation of spatial coherence across fronto-central regions. Such findings would suggest that CLAS can stabilize cortical δ-waves and counteract arousal-related desynchronization, thereby supporting anesthetic stability and analgesic protection.

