#### Procedures for SA3 (part 2)

2.2.3

Immediately following the completion of Part 1, a 6.5 min *in-phase* stimulation block will be initiated, with simultaneous hd-EEG and pain monitoring using the NOL index, mean arterial pressure and heart rate. The first minute of *in-phase* stimulation will be free of painful stimulation (*Pre-Pain*). A standardized nociceptive stimulation will then be delivered for 30 s (*Pain*). This will consist in a standardized tetanic stimulation to the ulnar nerve of the non-dominant forearm delivered by a routine nerve stimulator (100 Hz, 70 mA; Life Tech - EZstim II) for a duration of 30 s. Measurements will continue during 5 min following painful stimulation (*Post-Pain*). Upon completion, noise-blocking earmuffs, in-ear earphones, and the hd-EEG net will be removed, and study team will exit the operating room. Surgery will begin and anesthetic procedures will continue as standard of care.

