### EEG pre-processing

3.1

EEG data will be preprocessed using a custom MNE Python script and will be bandpass filtered from 0.1 to 50 Hz. Non-scalp, noisy channels, and channels overlapping with the BIS monitor will be removed. EEG data will be re-referenced to an average reference. Data will then be segmented into the 6 conditions of study: (1) *In-phase*; (2) *Anti-phase*; (3) *sham*; (4) *Pre-Pain*; (5) *Pain*; (6) *Post-Pain*.

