#### CLAS and nociceptive stimulation

3.7.3

Because nociceptive stimulation will be delivered only during *in-phase*, the primary analyses will assess within-subject changes across the *Pre-Pain*, *Pain*, and *Post-Pain* epochs. As a first step, *δ*-wave morphology will be quantified by comparing amplitude, slope, and power spectral density (PSD) across the three conditions, since these features provide sensitive markers of cortical arousal and nociceptive disruption under anesthesia (Bonhomme et al., 2016; Plourde et al., 2006). To dissociate band-limited power changes from broadband spectral shifts that can occur under propofol anesthesia, we will additionally parameterize the aperiodic (1/f-like) component of the EEG power spectrum for each stimulation block. Power spectral density will be estimated per block and channel, and the aperiodic exponent (slope) and offset will be extracted over a predefined frequency range using spectral parameterization methods. These aperiodic parameters will be compared across *in-phase, anti-phase*, and *sham* conditions and, where relevant, included as covariates when interpreting *δ*-band power changes.

The primary analysis of nociceptive reactivity will be changes in the NOL index and time-to-recovery. Secondary analysis will examine changes in mean arterial pressure (MAP), heart rate (HR), and BIS index values. Source localization and propagation analyses will further characterize the cortical generators and spatiotemporal spread of δ-waves during nociception (Massimini et al., 2004; Murphy et al., 2011).

Statistical models will include linear mixed-effects analyses with Condition (*Pre-Pain*, *Pain*, *Post-Pain*) as a fixed factor and age, and sex. *p*-values will be corrected for multiple comparisons using familywise error correction. This design enables testing whether *in-phase* CLAS can preserve *δ*-wave integrity and stabilize autonomic reactivity in the presence of nociceptive input, a key criterion for balanced anesthesia (Garcia-Larrea and Bastuji, 2018).

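### The SA3 model has no stimulation-off reference, so it cannot tell a CLAS effect that survives pain from no CLAS effect at all

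*Protocol article*

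**What the plan says.** Section 1.8 of the protocol article sets the secondary objective: whether the modulatory effects of in-phase CLAS on δ-waves "during general propofol anesthesia are preserved in the presence of nociceptive inputs".

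Section 3.7.3 gives the model: "Statistical models will include linear mixed-effects analyses with Condition (*Pre-Pain*, *Pain*, *Post-Pain*) as a fixed factor and age, and sex". Its opening explains the restriction to these epochs: "Because nociceptive stimulation will be delivered only during" in-phase CLAS. Section 2.2.3 confirms that the three epochs (1 min, 30 s, 5 min) lie inside one continuous in-phase run: "Immediately following the completion of Part 1, a 6.5 min" block begins.

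Sham is the no-stimulation baseline (section 2.1.3). It is recorded in Part 1 only, without pain. Section 3.1 already cuts it out as a separate segment: "Data will then be segmented into the 6 conditions of study", sham being one of the six. Section 3.7.1 uses it for the SA1 δ-wave comparison. In section 3.7.3 it appears only for the aperiodic parameters, never against a pain epoch.

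Section 3.7.3 nevertheless closes by saying that the design can test whether in-phase CLAS keeps δ-waves intact under nociception. Section 4.3 states the matching hypothesis against pain given without CLAS, a condition that is not recorded.

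**The concern.** The objective is about an effect of stimulation, and such an effect is a difference between stimulation on and stimulation off. The SA3 model contains only stimulation-on epochs. It describes how δ-waves respond to a painful stimulus while CLAS runs, but no term in it measures what CLAS contributes.

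This matters because a null CLAS effect is a live possibility. Section 1.7 says it is unknown whether CLAS enhances slow-wave activity under propofol, and section 4 says the predictions are not empirically informed. Nothing in the article makes the SA3 conclusion depend on an in-phase effect having been shown. A small δ-wave response to the stimulus could then be read as support for preservation even if there was nothing to preserve.

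**Working it through.** There is no stated figure to reproduce: section 2.1.2 gives 30 patients, justified by feasibility, prior literature and the within-subject design, with no effect size, SD or margin.

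**Notation.** m = δ level with neither CLAS nor pain; c0 = CLAS effect without pain; c1 = CLAS effect during pain; p = effect of pain itself.

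**Expected contrasts.**
- Sham = m; Pre-Pain = m + c0; Pain = m + p + c1.
- Pain − Pre-Pain = p + (c1 − c0).
- Pre-Pain − sham = c0.
- Pain − sham = p + c1.

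If the effect is fully kept (c1 = c0), the SA3 contrast is p whatever the size of c0, including zero. The same holds for Post-Pain − Pre-Pain. An equivalence margin would not help, because the expected value is the same in both cases. The contrast also mixes two causes: p = −0.8 with c0 = c1 = 1, and p = 0 with c0 = 1 and c1 = 0.2, both give −0.8.

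**Simulation of the cancellation.** 30 patients, 20,000 runs, paired tests at two-sided 0.05; residual SD 1, subject SD 2, effects in residual SDs (all assumed).

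| c0 = c1 | p | Pain vs Pre-Pain non-significant | Pre-Pain > sham significant |
|---|---|---|---|
| 0 | 0 | 94.8% | 2.6% |
| 1 | 0 | 94.9% | 96.0% |
| 0 | −0.8 | 15.2% | 2.5% |
| 1 | −0.8 | 15.0% | 96.3% |

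The SA3 column does not separate a zero effect from a kept one; the sham column does.

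**What sham cannot supply.** Pain − sham is p + c1, so c1 is not identified. With c0 = c1 = 1 and p = −0.8 it is only 0.2, and it is significantly positive in 11% of runs although the effect is fully kept. A retained share, (Pain − sham)/(Pre-Pain − sham), equals (p + c1)/c0. With c0 = c1 = 0.6 and p = −0.4 it is 0.2/0.6 = 0.33, although true retention is 100%.

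**Drift.** Section 2.2.2 allows that anesthesia may deepen slowly despite stable infusion. Assume the listed order, two 20-s pauses and none before Part 2. Midpoints are then in-phase 1.5 min, sham 8.17, Pre-Pain 10.17, Pain 10.92 and Post-Pain 13.67. For an assumed linear drift of 0.1 SD of a paired difference per minute, in the direction of stronger δ-waves:
- In-phase − sham (Part 1): 1.5 − 8.17 = −6.67 min, a shift of −0.67 SD.
- Pre-Pain − sham: 2.0 min, +0.20 SD.
- Pain − sham: 2.75 min, +0.275 SD.
- Post-Pain − sham: 5.5 min, +0.55 SD.

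With CLAS and pain effects both zero, Pain > sham is then significant in 31% of trials, against about 2.5% without drift. In the other direction, a true in-phase effect of 0.6 SD would appear in Part 1 as 0.6 − 0.67 = −0.07 SD.

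**The case against.** Three arguments on the other side have weight.

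First, the article gives no decision rule for preservation, and its expectations are not of a flat result: section 1.8 expects a weaker enhancement under pain, and section 4.3 a faster recovery. A reader might infer that a zero effect would be reported as preserved. The documents do not support that. The 94.8% is the rate of one non-significant contrast under assumed values, not the rate of a planned claim. What stands is that the contrast gives the same answer in both cases, whatever rule is later applied to it.

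Second, SA1 compares in-phase with sham in the same patients as the primary aim, so a null effect would be visible in the same report, and ordering of aims may be set in an analysis plan not shown here. This limits the damage but does not remove it. Section 3.7.3 states both the factor levels and the inference drawn from them. It does not tie that inference to SA1, and Pre-Pain is never compared with sham.

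Third, section 4.3 defines the SA3 effect against pain without CLAS, so sham is not the comparator named there. This is correct and limits the remedy. A reader might also take Pain minus sham as a safe lower bound on the CLAS effect under pain, since section 1.4 says that nociception "can transiently increase cortical responsiveness and disrupt ongoing SW dynamics". Drift works the other way, as the 31% shows, so that reading does not hold either.

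**Conclusion.** The point holds in a limited form. As specified in section 3.7.3, the SA3 contrasts cannot distinguish a CLAS effect of zero from one fully kept under pain, and so cannot by themselves support the statement that in-phase CLAS preserves δ-waves. This is algebraic and rests on no assumed size; only the simulated rates depend on the assumed SDs, effects and drift.

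Adding sham closes part of the gap: it can show whether an in-phase effect was present in Part 2 before the painful stimulus, subject to drift. It does not identify the CLAS effect under pain, because pain is never given without CLAS.

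**What to change.** In section 3.7.3:

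1. Make any statement that the effect is preserved conditional on an in-phase effect against sham being shown in the Part 1 (SA1) contrast. If none is shown, report SA3 only as the δ-wave response to the stimulus under CLAS.
2. Add the already segmented sham block as a reference level of Condition for the δ-wave metrics. Report Pre-Pain minus sham as supporting evidence that the effect is present in Part 2.
3. Report Pain minus sham and Post-Pain minus sham descriptively. State that they combine pain's own effect with the CLAS effect and that, with sham before Part 2 in the listed order, slow deepening could inflate them. Do not report a retained share.
4. State that the CLAS effect under pain, against pain without CLAS as in section 4.3, is not identified by this design.

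The cost is analysis wording only, with no new recording or procedure. The downside is a lower chance of making a preservation claim when the effect is real. Its size depends on effect sizes and drift that the documents do not give; the −0.07 SD example shows that strong drift could hide a real effect in Part 1.
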